## Abstract

**Background:**

Single-nucleotide variations (SNVs; formerly SNPs) are inherited genetic variants that can be easily determined in routine clinical practice using a simple blood or saliva test. SNVs have potential to serve as noninvasive biomarkers for predicting cancer-specific patient outcomes after resection of pancreatic ductal adenocarcinoma (PDAC). Two recent analyses led to the identification and validation of three SNVs in the CD44 and CHI3L2 genes (rs187115, rs353630, and rs684559), which can be used as predictive biomarkers to help select patients most likely to benefit from pancreatic resection. These variants were associated with an over 2-fold increased risk for tumor-related death in three independent PDAC study cohorts from Europe and the United States, including The Cancer Genome Atlas cohorts (reaching a *P* value of 1×10^–8^). However, these analyses were limited by the inherent biases of a retrospective study design, such as selection and publication biases, thereby limiting the clinical use of these promising biomarkers in guiding PDAC therapy.

**Objective:**

To overcome the limitations of previous retrospectively designed studies and translate the findings into clinical practice, we aim to validate the association of the identified SNVs with survival in a controlled setting using a prospective cohort of patients with PDAC following pancreatic resection.

**Methods:**

All patients with PDAC who will undergo pancreatic resection at three participating hospitals in Switzerland and fulfill the inclusion criteria will be included in the study consecutively. The SNV genotypes will be determined using standard genotyping techniques from patient blood samples. For each genotyped locus, log-rank and Cox multivariate regression tests will be performed, accounting for the relevant covariates American Joint Committee on Cancer stage and resection status. Clinical follow-up data will be collected for at least 3 years. Sample size calculation resulted in a required sample of 150 patients to sufficiently power the analysis.

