**Conclusions:**

This is the first prospective study of the *CD44* and *CHI3L2* SNV–based biomarker signature in PDAC. A prospective validation of this signature would enable its clinical use as a noninvasive predictive biomarker of survival after pancreatic resection that is readily available at the time of diagnosis and can assist in guiding PDAC therapy. The results of this study may help to individualize treatment decisions and potentially improve patient outcomes.

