A growing body of evidence suggests that inherited genetic variants can also be used to predict cancer-specific patient outcomes and guide therapy for patients with pancreatic cancer. Specifically, in a retrospective analysis, we identified a germline variant in the CD44 gene (rs187115) that can serve as a predictive biomarker to help select patients who are likely to benefit from pancreatic resection [9,10]. More recently, we performed a genome-wide screen for inherited variants that affect survival in patients with PDAC based on existing biological knowledge about the regions where the genetic variants reside [11]. This search for high-frequency polymorphic variants that affect tumor-related survival and either result in an altered protein structure and function or reside in known regulatory noncoding genomic regions has identified two clinically relevant sequence variants in functional regions of genes that are known to regulate cancer progression, invasion, and metastasis [11]. Specifically, regulatory variants within *CHI3L2* (rs684559) and *CD44* (rs353630) were found to be associated with an over 2-fold increased risk of tumor-related death in two independent retrospective PDAC study cohorts from Europe and the United States (hazard ratio [HR] 0.38, 95% CI 0.27-0.53; *P*=1×10^–8^, q value<.05) [11].

Taken together, these retrospective studies have demonstrated the potential of polymorphic sequence variants to identify a subset of patients with high-risk pancreatic cancer associated with a very low survival probability that might be eligible for inclusion in clinical trials of new therapeutic strategies, including neoadjuvant chemotherapy protocols and novel adjuvant systemic regimens. In addition, the findings from these studies suggest that the biological knowledge about these SNVs could help guide the development of such individualized genomic treatment strategies.

However, despite their robustness, the described results have not yet been validated prospectively and it is unclear whether these observations can be independently replicated in a controlled clinical setting.

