### Power of the Study

Sample size calculations were performed in G-Power 3.1 software (Heinrich-Heine University, Germany) based on the results of the previously mentioned retrospective studies according to the ability to detect an HR>2 between genotypes [9-11]. With the use of a two-sided α level of .05 and considering a dropout rate of 10% as well as a potential additional error margin of 10%, 150 patients are required to obtain 80% power to detect a difference in cancer-related survival between genotypes.

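### Three SNVs are tested separately, but the sample size covers one unspecified genotype comparison at an undivided .05 and the conclusion concerns a signature for which no test is described

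*Protocol article*

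**What the plan says.** The Background of the abstract names three variants for validation: rs187115 and rs353630 in CD44, and rs684559 in CHI3L2. Study Aim, Design, and Setting gives the aim as confirming their association with survival after resection. The primary endpoint, under Endpoints and Data Collection, is tumor-related survival.

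On the analysis, the Methods of the abstract state: "For each genotyped locus, log-rank and Cox multivariate regression tests will be performed", with stage and resection status as covariates. The Statistical Analysis section adds Kaplan-Meier curves with the log-rank test and Cox models. It gives no significance level, no primary locus and no order of testing.

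On size, Power of the Study bases the calculation on the retrospective work, "according to the ability to detect an HR>2 between genotypes". It continues "With the use of a two-sided α level of .05", allows 10% for dropout and a further 10% margin, and concludes that "150 patients are required to obtain 80% power to detect a difference in cancer-related survival between genotypes". It does not name the locus, the genotype grouping, the genotype frequency or the number of events.

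On the claim, the Conclusions of the abstract say: "A prospective validation of this signature would enable its clinical use as a noninvasive predictive biomarker of survival after pancreatic resection". The Discussion also speaks of a predictive signature.

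**The concern.** Three parts of the article concern three different hypotheses. The analysis is about each of three loci. The sample size is about one contrast between genotypes. The conclusion is about a signature. Nothing says which of these decides whether the validation has succeeded.

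This matters because the study exists to confirm known associations free of the selection that affects retrospective work. With the deciding hypothesis open, three rules are possible, and none matches what is stated:

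- Any significant locus suffices: the false-positive risk exceeds the stated alpha.
- All loci must replicate: the chance of success can be well below 80%.
- Alpha is divided among the loci: the power per locus is lower than stated.

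Under none of these rules has a combined signature been tested.

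**Working it through.** **Inputs from the article.** Three loci, two of them in CD44; two-sided alpha .05; power 80%; hazard ratio (HR) above 2, taken as 2; N = 150; 10% dropout and a further 10% margin; earlier estimate HR 0.38, which inverts to 1/0.38 = 2.63.

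**Assumptions, not in the article.** Genotype split, share of patients with an event, and correlation between the locus tests. Ranges are shown where they matter.

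**1. The stated N.** Schoenfeld events: d = (z for alpha/2 + z for power)² / [p(1−p)(ln HR)²]. At two-sided .05 and 80% power the numerator is (1.960 + 0.842)² = 7.849, and (ln 2)² = 0.4805.

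| Genotype split p | Events at .05 | Events at .05/3 |
|---|---|---|
| 50:50 | 65.3, so 66 | 87.2, so 88 |
| 25:75 | 87.1, so 88 | 116.2, so 117 |
| 20:80 | 102.1, so 103 | 136.2, so 137 |

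Freedman's formula for 50:50 gives 9 × 7.849 = 70.6, so 71. With the two 10% inflations, N at .05 runs from about 80 (50:50, every patient with an event: 66 × 1.21) to 258 (20:80, half with an event: 103/0.5/0.8). A 25:75 split with 70% events gives 151 to 158, depending on how the inflations are applied. So 150 is plausible for one comparison at .05, but it can be neither reproduced nor refuted.

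**2. Error if any locus counts.** With three independent tests at .05 and no true association: 1 − 0.95³ = 0.1426. If the two CD44 tests were perfectly correlated, there would in effect be two tests: 1 − 0.95² = 0.0975. Simulation with 10⁶ draws gives 13.6% at a correlation of 0.5 and 11.7% at 0.9. The CHI3L2 test is taken as independent throughout.

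**3. Power if alpha is divided.** A design with exactly 80% at .05 and HR 2 has an expected z of 1.960 + 0.842 = 2.802. The critical value at .05/3 is 2.394. Power = Φ(2.802 − 2.394) = Φ(0.408) = 0.658. To restore 80%, events rise by (2.394 + 0.842)²/7.849 = 10.469/7.849 = 1.33, so about 200 patients instead of 150. This ratio does not depend on the genotype split or event share.

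This is Bonferroni. Holm is never less powerful, so under Holm the power for a locus lies between 66% and 80%.

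**4. The same design at the earlier estimate.** Expected z = 2.802 × ln(2.63)/ln(2) = 2.802 × 0.968/0.693 = 3.911. Power at .05/3 = Φ(3.911 − 2.394) = Φ(1.517) = 0.935.

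**5. All three loci at .05.** At HR 2 with 80% each and independence: 0.8³ = 0.512. At HR 2.63 for every locus: Φ(3.911 − 1.960)³ = 0.974³ = about 0.925.

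**The case against.** The strongest reply is that this is a journal article. A separate analysis plan may exist, and multiplicity rules, allele coding and test order are usually placed there. That stands as far as it goes: a reader might infer that the trial has no error control, but the article shows only that none is described here. The silence is not the point. An unseen plan cannot make a one-comparison sample size at full .05 deliver 80% for three adjusted tests at HR 2, nor turn per-locus tests into a test of a signature.

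Other replies also have weight:

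- **The .05 appears only in the sample-size section.** Using it for each locus is a fair inference, not a statement. The article also never says that one significant locus counts as validation.
- **A reader might infer that the 80% power is wrong.** It is not shown to be. It can hold for one unadjusted locus at HR 2, and 150 lies inside the plausible range.
- **The power loss depends on the effect.** At 2.63 an adjusted test keeps more than 80%. But the article's own design target is an HR of 2, and its single estimate of 0.38 is given for rs684559 and rs353630, not separately for rs187115.
- **The Introduction gives HR 0.38 for variants that "were found to be associated with an over 2-fold increased risk of tumor-related death in two independent retrospective PDAC study cohorts".** A reader might take this as proof that the direction is open. The simplest explanation is the choice of reference genotype. It is a reason to state the reference, not evidence that the contrast will be picked after genotyping.
- **The aim concerns the individual SNVs, so per-locus tests fit it, and signature may be a collective label.** That is possible, and if so the conclusion should say so.
- **The log-rank and Cox tests need not compete.** The log-rank test accompanies the Kaplan-Meier curves, and the Cox model adds covariates.

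**Conclusion.** The concern holds as a mismatch within the article: separate tests of three loci, a sample size for one unnamed comparison at full .05, and a conclusion about a signature with no described test.

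Its size depends on the success rule, which is not stated:

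- **Any locus at .05:** family-wise error up to about 14%, and not below 9.75% if the CHI3L2 test is independent of the CD44 tests. A flat 14% would assume that all three tests are independent, although two loci lie in one gene.
- **Alpha split in three:** about 66% per locus for a design with exactly 80% at HR 2, and 93.5% if the true HR is 2.63.
- **All three at .05:** about 51% at HR 2 under independence.

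The article does not support saying that 150 is too few for a single comparison, or that several genotype codings will be tried. Nor does it show that the retrospective work contains a combined three-SNV score or cut-off that could simply be copied.

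**What to change.** Before any genotype is determined, name one primary hypothesis for tumor-related survival, tested in the Cox model adjusted for stage and resection status. State the risk genotype, reference genotype and direction for each SNV, carried over from the retrospective work. Then choose one of two routes:

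1. **One combined test.** Define in advance how the three SNVs are combined and test that at two-sided .05. Make the single loci secondary under Holm, and give the power for the combined contrast.
2. **Three co-primary loci.** Control them with Holm, and restate the power section per locus, in events, at the corrected alpha and with the assumed genotype split and event share.

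If no combined test is defined, word the conclusion for the individual loci and drop the claim of validating a signature.

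The cost is wording, since the article reports that no genotypes exist. No patients or procedures are added. Time is limited: 142 of 150 patients were recruited by November 2023, and genotyping follows the last inclusion. On the second route the stated power becomes less favourable: at HR 2 it could be as low as 66% per locus, and keeping 80% at .05/3 would take about 200 patients.

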## Introduction

Pancreatic ductal adenocarcinoma (PDAC) is the most frequent type of pancreatic cancer and one of the most lethal malignancies due to a tendency for early local invasion and high metastatic potential [1,2]. Despite this aggressive phenotype, PDAC shows a wide range of biological features, whereby early recurrence is observed in some patients who undergo pancreatic resection, whereas long-term cancer-free survival can be achieved in others [3-5]. It is considered that such individual oncologic courses and the response to personalized treatment plans can be predicted by gaining a more comprehensive understanding of human germline genetic variation [6,7]. Importantly, this genetic information can be found in the germline DNA and thus does not require a tumor biopsy or the technically demanding isolation of circulating tumor cells. Instead, samples can be easily obtained by a simple and cheap blood or saliva test at any time during diagnostic workup or treatment, offering a noninvasive predictive biomarker available at the time of diagnosis. Indeed, this type of personalized medicine is no longer a fantasy but a maturing reality. In other cancer types, including acute lymphoblastic leukemia, colorectal cancer, lung cancer, and breast cancer, the genotyping of certain single-nucleotide variations (SNVs; formerly SNPs) is recommended by the US Food and Drug Administration [8].

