## Methods

### Study Aim, Design, and Setting

This project is designed as a one-arm prospective controlled clinical study that aims to validate the association of the previously identified SNVs in the CD44 and CHI3L2 genes with PDAC survival after tumor resection. We aim to use a prospective cohort of patients with PDAC who will undergo pancreatic resection at our established network of three cantonal hospitals (Departments of Surgery at the Cantonal Hospital of Winterthur, Cantonal Hospital of Lucerne, and the Triemli Hospital in Zurich) in Switzerland. The study outline is depicted in Figure 1.

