### Endpoints and Data Collection

The primary endpoint of the study is tumor-related survival. Secondary endpoints include recurrence and overall survival. The exact type and timing for data and blood sample collection are detailed in Table 1. The estimated total duration of the study is 5 years, including the scheduled 3-year postoperative follow-up.

**Table 1 table1:** Type and timing of data and blood sample collection.

Data and timing of collection	Screening	Surgery	Early postoperative period	Follow-up
Visit	1	2	3	4, 5, and 6
Time	Preoperative	day 0	1 week postoperative	1, 2, and 3 years
Participant information and informed consent	✓			
Medical history	✓			
Inclusion/exclusion criteria check	✓			
Blood collection	✓			
Surgical procedure		✓		
Histopathological data			✓	
Recurrence/survival data				✓

All cases will be presented at interdisciplinary tumor board meetings at each participating center pre- and postoperatively. All patients will be offered standard-of-care multimodal treatment at the discretion of the interdisciplinary tumor board at each participating center. The operation will be performed according to the group assignment by senior surgeons only, who have extensive experience in pancreatic resections. All surgeries will be performed at the Departments of Surgery at the Cantonal Hospital of Winterthur, Cantonal Hospital of Lucerne, and the Triemli Hospital in Zurich. The follow-up of the patient will be recorded for at least 3 years after tumor resection. Data collection will be completed using the hospital records or by contacting the patient’s general practitioner or oncologist; thus, no additional appointments in the outpatient clinic will be required for study purposes.

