### Statistical Analysis

A parametric two-sided Student *t* test and a two-tailed Mann-Whitney *U* test will be used to compare data distributions in groups with normally distributed data and data that deviate from a normal distribution, respectively. The Fisher exact test will be used to calculate frequency distributions in cross-table analyses. Kaplan-Meier survival curves (log-rank test) and Cox proportional hazards models will be calculated to assess and compare survival times. All statistical analyses will be performed using R and SPSS software.

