## Discussion

This is the first prospective study of the clinical value of *CD44* and *CHI3L2* SNV–based biomarkers in PDAC after tumor resection. The design of this study enables minimizing the biases inherent in retrospective trials, such as selection or publication biases. Moreover, akin to a randomized controlled trial designed to compare clinical interventions, both the study participants and all physicians involved in the treatment of the included patients will be fully blinded by determining the SNV genotypes and analyzing the results only after the completion of follow-up of all patients. Such a prospective validation of these biomarkers would allow for their clinical use as a predictive signature of survival after pancreatic resection that can be readily available at the time of PDAC diagnosis.

The main limitation of the study is the heterogeneity of the patient group with regard to the neoadjuvant and adjuvant treatment(s) the individual participants will receive. These treatments are known to affect patient outcomes, including cancer-related survival as the main endpoint of this study. However, this heterogeneity also reflects real-world clinical practice and should thus provide a robust biomarker that can be applied to all patients with PDAC who undergo resection of their tumors, regardless of the chemoradiotherapy they individually receive. Another limitation is the disruption of administrative and processes during the COVID-19 pandemic. However, since patients diagnosed with pancreatic cancer received adequate treatment without major delays and were included consecutively in this study during this disruptive period, the effect on the study results should be negligible.

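### Stratifying the survival analysis by hospital, in addition to stage and resection status, would be a near-free improvement while no genotypes are known

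*Protocol article*

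**What the plan says.** The covariates are named in one place, the Methods part of the Abstract, where each genotyped locus is tested by log-rank and Cox regression, "accounting for the relevant covariates American Joint Committee on Cancer stage and resection status". The Statistical Analysis section adds none: "Kaplan-Meier survival curves (log-rank test) and Cox proportional hazards models will be calculated to assess and compare survival times".

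The cohort comes from "our established network of three cantonal hospitals" (Study Aim, Design, and Setting). On treatment, Endpoints and Data Collection states: "All patients will be offered standard-of-care multimodal treatment at the discretion of the interdisciplinary tumor board at each participating center". The Discussion gives differing neoadjuvant and adjuvant treatment as the main limitation. It says that such treatment influences cancer-related survival, and it accepts the variation as a reflection of ordinary practice.

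The Introduction stresses that "this genetic information can be found in the germline DNA", and the Discussion says that "both the study participants and all physicians involved in the treatment of the included patients will be fully blinded by determining the SNV genotypes" only later. The Results report that no genotype had been determined and no analysis done.

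**The concern.** Hospital is known for every patient. It may stand in for several things that can shift survival: the local board's treatment choices, the surgical team, and how recurrence and cause of death are traced through local records and practitioners. The plan supplies the link itself, since boards decide treatment centre by centre and treatment affects the endpoint. Yet hospital is not among the covariates called relevant.

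Two things could follow, and they need different conditions.

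- **Attenuation.** If baseline hazard differs by hospital, a Cox model without hospital estimates a genotype hazard ratio nearer to 1, even when genotype is balanced across hospitals. The test then loses some power.
- **Bias under the null.** If carrier frequency also differs by hospital, in line with hazard, part of the hospital difference is read as a genotype effect. There is no randomisation to balance genotype across hospitals.

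**Working it through.** **The plan's own figure.** Power of the Study asks for 150 patients for 80% power, two-sided alpha 0.05, "according to the ability to detect an HR>2 between genotypes", with 10% for dropout and a further 10% margin. Schoenfeld's formula for the number of events is

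d = (1.960 + 0.842)² / [p(1 − p)(ln 2)²], where p is the carrier share.

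This gives 66 events at p = 0.50, 78 at 0.30, 88 at 0.25 and 103 at 0.20. Dividing by the event proportion and by 0.9 × 0.9 = 0.81:

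- p = 0.50 with 55% events: 66 / 0.55 / 0.81 = 148 patients
- p = 0.25 with 75% events: 88 / 0.75 / 0.81 = 145 patients

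So 150 is attainable under some assumptions. It can be neither confirmed nor refuted, because the article states neither carrier share nor event proportion.

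**Inputs from the article.** Hazard ratio 2; two-sided alpha 0.05; three hospitals; 150 × 0.81 = about 122 evaluable patients; 3 years of follow-up.

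**Inputs assumed.** Exponential survival with a non-carrier median of 1.8 years; equal hospital sizes; censoring of everyone at 3 years; the carrier shares and hospital hazards shown below. Stage and resection status are not modelled.

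**Power at hazard ratio 2, same carrier share in every hospital** (Cox model, 2,000 simulated trials per row, Monte Carlo error about 1 point):

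| Hospital hazards | Carriers | HR without hospital | Power without hospital | Power stratified |
|---|---|---|---|---|
| 1/1/1 | 30% | 2.01 | 87.9% | 86.9% |
| 0.8/1/1.25 | 30% | 1.97 | 86.5% | 86.7% |
| 0.67/1/1.5 | 30% | 1.92 | 83.8% | 88.0% |
| 0.5/1/2 | 30% | 1.79 | 73.0% | 84.3% |
| 1/1/1 | 20% | 2.03 | 80.4% | 79.3% |
| 0.8/1/1.25 | 20% | 1.98 | 77.3% | 76.7% |
| 0.67/1/1.5 | 20% | 1.94 | 73.5% | 77.3% |
| 0.5/1/2 | 20% | 1.83 | 65.6% | 77.5% |

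The gain of 4.2 points at 0.67/1/1.5 with 30% carriers is on the high side of simulation noise. The stratified power there (88.0%) exceeds that with no hospital effect (86.9%), which is not a real feature. A longer run under the same assumptions (8,000 trials, both models fitted to the same data) gives 84.1% against 86.7% at 0.67/1/1.5, a gain of 2.6 points. At 0.6/1/1.6 it gives 81.2% against 86.5%, a gain of 5.3 points. About 2 to 4 points and about 5 points are fair summaries. Gains of 11 to 12 points appear only at 0.5/1/2, a fourfold spread.

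**Rejection rate with no genotype effect** (2,000 trials per scenario, hazards from 0.8/1/1.25 to 0.5/1/2):

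| Carrier share by hospital | HR without hospital | Rejection without hospital |
|---|---|---|
| 30/30/30% | 1.00 | 4.8 to 5.9% |
| 25/30/35% | 1.04 to 1.11 | 6.4 to 7.7% |
| 20/30/40% | 1.08 to 1.22 | 6.0 to 13.8% |

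The stratified model rejects 4.2 to 5.4% of the time throughout. With hazards no wider than 0.67/1/1.5, the highest unstratified rate is 9.5%. Equal carrier shares give no inflation, however far the hospital hazards differ.

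**The case against.** The strongest reply is that this is a condensed article. The full analysis plan is not shown and may already hold a centre term, and naming two covariates does not rule one out. That stands against calling the matter an error. It does not remove the suggestion, because the article says which covariates it regards as relevant and hospital is not one of them. If the full plan has the stratum, nothing more is needed.

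A reader might draw four stronger conclusions that the documents do not support.

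- **That confounding is present.** Confounding needs hospital to be linked to both survival and genotype. Local treatment decisions supply at most the first link. Genotype is inherited and unknown to the boards, so they cannot treat by it. Nothing in the article suggests that carrier frequency differs among three Swiss hospitals. Nothing excludes it either, since blinding does not equalise allele frequencies between catchment areas.
- **That power is certainly lost.** No hospital difference in survival is reported. The Discussion speaks of variation between individual patients, and the step to variation between hospitals is an inference. All centres offer standard care with experienced senior surgeons.
- **That the sample size has little margin.** Carrier share and event proportion are not given, and the calculation includes an explicit extra 10%.
- **That the lower hazard ratio is a bias.** With genotype unrelated to hospital, the shift toward 1 is the difference between a marginal and a conditional hazard ratio. It reduces power but does not distort the test under the null.

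Two limits of the simulation also stand. Only hospital differences that remain after adjustment for stage and resection status matter, and those covariates were left out. Censoring everyone at 3 years probably understates events, because follow-up is at least 3 years.

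**Conclusion.** The point holds as a recommended refinement of a stated analysis. Under the assumed inputs, stratifying by hospital gains between nothing and about 5 points of power for hazard spreads up to 0.6/1/1.6, and more only if hospitals differ very strongly. If hospitals do not differ, it costs about 1 point. It also holds the rejection rate near 5% if carrier frequency should follow hospital hazard, a situation in which the unstratified test would reject about 6 to 10% of the time at moderate spreads. The balance favours stratifying, but the size of the benefit is unknown because the article reports neither survival nor genotype frequency by hospital.

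**What to change.** Before any genotyping, add a sentence to the Statistical Analysis section: the log-rank test and the Cox models for tumor-related survival, recurrence and overall survival are stratified by hospital (three strata), and the Cox models also include AJCC stage and resection status.

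The cost is that sentence and one term in the code. No new data are needed. The timing matters: with no genotypes determined, this is clean pre-specification, whereas adding the stratum once genotypes are linked to outcome would be a post hoc choice in a study meant as an unbiased validation.
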